### 10.2 Secondary study parameter(s)

Mixed models with intention-to-treat will be used to compare EMDR and waiting list qua (1) the decline of diagnoses of PD, (2) the severity of psychotrauma and PTSD symptoms and (3) the severity of difficulties in emotion regulation and interpersonal functioning. The economic evaluation will be undertaken according to the Dutch guidelines for costs effectiveness studies taken a societal perspective (Hakkaart et al., 2016). The severity (i.e., number of symptoms) of PD, aided by the ADP-IV, will be used for effectiveness. The TiC-P is used to collect data on utilization of medical services and productivity loss. Utility scores are estimated using the EQ-5D-5L and MHQoL will measure the effects. A cost-utility analysis and a cost-effectiveness analysis (CEA) are conducted. The cost-utility is calculated as the incremental costs and utilities, which yields a cost per QALY estimate. The cost-effectiveness is expressed in the incremental costs and scores on the SCID-5-PD.

Multilevel modeling is used to model cost-effectiveness. For assessing the uncertainty, cost effectiveness acceptability curves and cost effectiveness planes will be created after bootstrapping. The acceptability curve illustrates the probability that the cost-effectiveness ratio will be accepted for different thresholds. In a cost-effectiveness plane, both incremental costs and incremental effects are plotted to account for combinations.

Sensitivity analyses will be performed after the analysis if necessary.

Qualitative data on patients' experiences with EMDR therapy will be summarised by the researchers and provided to participants for respondent validation. The researchers will

thoroughly read all transcripts, highlight all potentially relevant excerpts and sort them based on the research questions. These sorted data will then be independently coded by the researchers; excerpts will be grouped based on their similarities. Then, these groupings will be identified/themed. Consequently, the researchers will confer and attempt to reach consensus on all groupings and themes, resulting in a preliminary codebook. The codebook and two information rich transcripts as examples will be presented to the study group. Themes will be reviewed, focussing on understanding the data and confirming that the data still correspond to the assigned themes.

### **10.3 Other study parameters**

Sample characteristics will be collected, presented and used in a regression analysis to explore individual predictors of success with EMDR.

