### **3. STUDY DESIGN**

To assess the surplus value of EMDR compared to waiting list, a single-blind RCT with two groups (EMDR versus waiting list) will be performed. The experimental group will receive ten bi-weekly EMDR sessions of ninety minutes each (with a total duration of 5 weeks). Data will be collected at baseline, 5 weeks (post EMDR-treatment) and three-, six- and twelve-months after onset of the study.

Based on a feasibility analysis, inclusion of patients will take 1 year.

The study will be conducted at Parnassia Psychiatric Institute and GGZ Delfland.

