### 4.4 Sample size calculation

In order to test the effectiveness of EMDR in reducing the number of PD symptoms over time, relative to waiting list, a linear mixed model (LMM) with intention-to-treat will be used. The RCT of five EMDR sessions revealed an effect size of 0.65 for change in psychological symptoms (Brief Symptom Inventory), 0.62 for psychological functioning (Outcome Questionnaire-45) and 0.56 for change in personality functioning (General Assessment of Personality Disorder) (Hafkemeijer et al., 2020). Since change in personality functioning is also (primarily) assessed in the current study, although with the aid of a different measure (ADP-IV), the effect size for the main analysis is expected to approximate the effect size found by Hafkemeijer et al., 2020. With the aid of standardization by post score standard deviations (standard procedure for meta-analyses) this effect size decreases to 0.46. Therefore, an effect size of 0.43 was estimated to be appropriate for this study. Using Liu and Liang's (1997) equation, assuming a correlation of 0.7 between five repeated measurements, a treatment effect size of 0.43, a power of 0.8, an  $\alpha$  significance level of .05, and two treatment conditions, the power analysis

resulted in a total sample size of 132 persons. With an estimated dropout rate of 20% a total of 159 patients is needed. With participation of 6 departments within two institutions our estimation is that it is feasible to include this number of patients within one year.

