## **5. TREATMENT OF SUBJECTS**

### **5.1 Investigational product/treatment**

Control condition: Participants in the waiting list condition will be seen once by a study therapist and informed about the course of the study. After three months patients will be offered the opportunity of following a standard treatment for their PD. This period is shorter than the regular waiting time for treatment of PD, which ranges 6 to 12 months.

Experimental condition: The Dutch version of the standard EMDR protocol (de Jongh & ten Broeke, 2019) will be used. The protocol will focus on the most distressing target memory. A total of 10 biweekly sessions of EMDR will be applied with a duration of 90 minutes per session. EMDR therapists are psychologists who have followed at least the basic EMDR training certified according to the guidelines of EMDR Europe. Group supervisions will be provided monthly by consultants in the treatment of EMDR. Additional supervision by telephone or e-mail is available on request. The treatment sessions will be videotaped; 10% will be randomly selected and rated by trained and blinded raters for therapist competence and treatment protocol adherence.

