#### 8.1.3 Other study parameters (if applicable)

- Broad demographic data will be collected to explore which patient will (not) benefit from EMDR.

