### 10.1 Primary study parameter(s)

The primary study parameter is the number of diagnosed PD symptoms, over five moments of measurement. In order to test the effectiveness of EMDR in reducing the number of PD symptoms over time, a linear mixed model (LMM) with intention-to-treat will be used. Within-subjects factor 'Time' has five levels (baseline vs. post-intervention vs. three-month vs. six-month vs. twelve-month follow-ups) and between-subjects factor 'Group' has two (EMDR vs. waiting list). Corrected post-hoc analyses will be performed where significant effects are found.

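### As worded, the section 10.3 regression on success with EMDR cannot separate patients who benefit from EMDR from those who would improve in either arm

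*Protocol*

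**What the plan says.** Two short statements bear on the point. Section 8.1.3 gives the purpose: "Broad demographic data will be collected to explore which patient will (not) benefit from EMDR". Section 10.3 gives the method: sample characteristics are to be "used in a regression analysis to explore individual predictors of success with EMDR". Section 10.3 does not name the arm or arms analysed, define success, or mention a characteristic-by-group interaction.

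The randomised comparator is available, since section 3 states that "a single-blind RCT with two groups (EMDR versus waiting list) will be performed". Section 5.1 says of the waiting-list condition: "After three months patients will be offered the opportunity of following a standard treatment for their PD". What these patients are later offered is therefore standard treatment, and nothing in the protocol offers them EMDR.

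The models in sections 10.1 and 10.2 compare the two groups explicitly, but neither contains a term that lets the group difference vary with a baseline characteristic.

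**The concern.** Who benefits from EMDR is a question about differences in treatment effect. Who does well after EMDR is a question about outcome in treated patients. Improvement in the EMDR arm combines the effect of EMDR with natural course, regression to the mean and general prognosis, and a model fitted in that arm alone cannot take these apart.

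Two errors follow if the result is read as an answer to section 8.1.3. A characteristic that predicts improvement equally in both arms would be reported as marking patients who benefit from EMDR. A characteristic that truly changes the EMDR effect could go unnoticed if it also predicts outcome in the opposite direction. The waiting-list data that would separate the two are already being collected.

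**Working it through.** **Inputs from the protocol (section 4.4).** The effect size is 0.43 ("an effect size of 0.43 was estimated to be appropriate for this study"). The correlation is 0.7 ("assuming a correlation of 0.7 between five repeated measurements"). Power is 0.80 and alpha 0.05. The total is 132 before dropout and 159 after.

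**Assumptions not in the protocol.** Allocation is 1:1, tests are two-sided, prognostic correlations are 0.2 to 0.4, a binary characteristic splits 50/50, and the residual variance v lies between 0.76 and 1.0.

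**Step 1: the plan's own figure.** Section 10.3 states no number, so the check starts from 132. For a time-averaged difference between two groups:

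n per arm = 2 (1.96 + 0.8416)² f / 0.43², with f = (1 + (m − 1) × 0.7) / m.

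- m = 5: f = 0.76, n = 64.5, so 65 per arm and 130 in total.
- m = 4: f = 0.775, n = 65.8, so 66 per arm and 132 in total.

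The stated figure reproduces to within two patients, or exactly with m = 4. Arm sizes are then 132/2 = 66 and 159/2 = 79.5, or about 80.

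**Step 2: regression in the EMDR arm only.** Take a characteristic that correlates r with improvement in both arms and has no influence on the EMDR effect. The chance that it is significant in the EMDR arm is approximately Φ(atanh(r) √(n − 3) − 1.96).

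| r | n = 66 | n = 80 |
|---|---|---|
| 0.2 | 36% | 43% |
| 0.3 | 69% | 78% |
| 0.4 | 92% | 96% |

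For example, r = 0.3 and n = 66 give 0.3095 × 7.937 = 2.457, and Φ(0.497) = 0.69.

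**Step 3: the same characteristic with an interaction test.** In 5,000 simulated trials with 66 per arm, the EMDR-only regression flagged the characteristic in 36%, 69% and 92% of trials at r = 0.2, 0.3 and 0.4, which agrees with step 2. The Group by characteristic interaction fitted in both arms flagged it in 4.9%, 5.5% and 4.8%.

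**Step 4: the opposite error.** With a true modifying effect of 0.30 SD per SD of the characteristic, offset by an opposite prognostic effect of the same size, the EMDR-only regression detected it in 5% of simulated trials and the interaction test in 42%.

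**Step 5: what the interaction test can deliver.** With a 50/50 split, the difference between two subgroup effects has SE = 4 √(v/N). With N = 132:

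- v = 0.76 (mean of five assessments): SE = 0.304. Power for an interaction of 0.43 is Φ(0.43/0.304 − 1.96) = 29%. The smallest interaction detectable with 80% power is 2.80 × 0.304 = 0.85 SD.
- v = 1.0 (one assessment): SE = 0.348. Power is 23%, and the smallest detectable interaction is 0.98 SD.

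The mean of the two post-baseline assessments up to three months has v = (1 + 0.7)/2 = 0.85, which lies inside this range. Powering an interaction of 0.43 would need 16 v (2.80)²/0.43², or about 517 to 680 analysed patients.

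These figures make no allowance for baseline adjustment. At the plan's correlation, adjustment would reduce v to 1 − 0.7² = 0.51 for one assessment (SE 0.249, power about 41%) or to 0.85 − 0.49 = 0.36 for the mean of two (SE 0.209, power about 54%). Both remain well short of 80%.

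**The case against.** The strongest objection is that section 10.3 never says the waiting list is left out. A model in both arms with interaction terms is compatible with its single sentence, and the choice of arms, time point and model terms for an exploratory regression is commonly left to a SAP, which is not at hand. This stands in part: a reader might infer that the protocol commits to dropping the control arm, and the text does not support that. What remains is that the protocol fixes the target as success with EMDR. That outcome has no counterpart in a group never given EMDR, and a SAP that followed the wording would answer a different question from the one in section 8.1.3.

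A second objection is that describing which treated patients do well is legitimate, and that the percentages in step 2 are simply power to detect a real association. This is correct. They are error rates only when the association is read as showing who benefits, which is the reading that section 8.1.3 invites.

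A reader might also infer that patients would be selected for or refused EMDR on these results. The protocol contains no such rule. The analysis is exploratory, stands under other study parameters, and is not among the primary or secondary objectives in section 2.

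Finally, the interaction test would rarely give a firm answer in this trial. That also stands, and it belongs in the report. A wide interval for the right quantity is still preferable to a significant result for a different one.

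**Conclusion.** The point holds as a mismatch between stated aim and stated method. Section 10.3, read with section 8.1.3, most naturally describes a predictor analysis within the EMDR arm, and such an analysis cannot distinguish prognosis from modification of the EMDR effect. A purely prognostic characteristic would be flagged in about 36% to 96% of trials, against about 5% with an interaction test. That range rests on assumed 1:1 allocation with 66 to 80 patients per arm and on assumed correlations of 0.2 to 0.4, none of which the protocol states. The documents do not support the stronger reading that the waiting list is definitely excluded or that treatment decisions will follow. Because the analysis is exploratory and the primary and secondary comparisons are untouched, this is a minor-to-moderate improvement.

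**What to change.** In section 10.3, state that the exploratory model is fitted in both arms, on an outcome measured in both, with a Group by characteristic interaction. Use assessments up to three months, before controls may start standard treatment. Report interaction estimates with confidence intervals and label them exploratory. If an EMDR-only regression is kept, call its associations prognostic and not evidence of who benefits. If it is to be the only analysis, reword section 8.1.3 to match.

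The cost is a sentence or two and one model term per characteristic, with no new data. Two limitations should be stated. Power is low, as shown in step 5: without baseline adjustment, the smallest interaction detectable with 80% power is about 0.85 to 0.98 SD, roughly twice the planned main effect. The six- and twelve-month data also do not give a clean untreated contrast for this question, so the interaction analysis cannot speak to later benefit.

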### **10.4 Interim analysis**

NA

## 11. ETHICAL CONSIDERATIONS

### 11.1 Regulation statement

The present study will be conducted according to the principles of the Declaration of Helsinki (World Medical Association, 2013) and in accordance with the Medical Research Involving Human Subjects Act (WMO).

### 11.2 Recruitment and consent

Recruitment will be at GGZ Delfland and multiple institutions of Parnassia Psychiatric Institute. Patients will be recruited in two ways. 1. By means of posters hanging in the waiting room; patients can announce themselves to their treating therapist/physician or the investigator. 2. Patients with the relevant diagnosis will be informed by their therapist/physician about the research. If the patient is interested, the therapist/physician informs the researchers, who will call the patients to invite them for an appointment. At this appointment, the researchers will provide the patients with further information and check eligibility for inclusion. If patients meet the inclusion criteria, they will receive the informed consent form, which they are allowed to sign right away, or whenever they feel ready. The written, informed consent of the patient will be collected by the researcher.

### 11.3 Objection by minors or incapacitated subjects

NA

### 11.4 Benefits and risks assessment, group relatedness

Patients with PD suffer from low self-esteem, have severe impairments in the regulation of emotions and interpersonal functioning and their quality of life is low. In a recent study, EMDR reduced BPD symptoms (De Jongh et al. 2020). In another study, psychological symptoms, psychological functioning, and personality functioning were positively affected by 5 EMDR sessions in all PDs (Hafkemeijer et al., submitted for publication). Thus, it is expected that patients who receive EMDR, will experience a reduction in PD symptoms and an improvement in psychological and personality functioning. In addition, EMDR is safe and not associated with an increase of self-injurious behaviour, suicidal gestures, suicides or hospital admissions. is applied in addition to treatment as usual for PD with regular meetings. In case emotions or traumatic intrusions increase in the two or three days after a session of EMDR, patients have the opportunity to discuss their symptoms with the EMDR- and PD-therapists. Also, no risks are expected due to the data collection.

The study requires participants in the control group to not receive treatment for three months. If necessary or if the participant no longer wants to participate, he or she is free to terminate participation.

With participation into this study, patients contribute to knowledge about treatment and can therefore contribute to the quality of treatment.

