## SUMMARY

**Rationale:** There is evidence suggesting that EMDR therapy is not only effective in the treatment of patients with personality disorders (PD) with and without PTSD, but also efficient, and thus cost-effective. Interventions for PD have a long duration and approximately 50% does not benefit sufficiently. The next step is to conduct a RCT for patients with all types of PD to explore the efficacy and cost-effectiveness of EMDR compared to waiting list to confirm these preliminary results.

**Objective:** The aim of this study is to evaluate the effectiveness of EMDR in reducing PD symptoms.

**Study design:** A multicenter, single-blind randomized controlled trial (RCT) with two arms: EMDR and no treatment (waiting list).

**Study population:** Patients with PD of eighteen years or older

**Intervention (if applicable):** The Dutch version of the standard EMDR protocol (de Jongh & ten Broeke, 2019) will be used. The protocol will focus on the most distressing target memory. A total of 10 biweekly sessions of EMDR will be applied with a duration of 90 minutes per session.

**Main study parameters/endpoints:** Mixed models, cost-utility and –effectiveness analyses will be conducted. The following outcome measures will be used: The Assessment van DSM Persoonlijkheidsstoornissen-IV and Clinician-Administered PTSD Scale for DSM-5 (primary outcomes) and the Structured Clinical Interview for DSM 5 Personality Disorders, Jeugd Trauma Vragenlijst, Life Events Checklist for the DSM-5, Level of Personality Functioning Scale - Brief Form 2.0, Clinician-Administered PTSD Scale for DSM-5, PTSD Check List, , Difficulties in Emotion Regulation Scale, Brief State Paranoia Checklist, Outcome Questionnaire-45, Euro-Quality of Life 5 dimension 5 level version, Treatment inventory Cost In Psychiatric Patients, Mental Health Quality of Life questionnaire.

Data will be collected at baseline, 5 week (post EMDR-treatment) and 3, 6 and 12 months after onset of the study.

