## 4. STUDY POPULATION

### 4.1 Population

Participants will be recruited from outpatient clinics of the Parnassia Psychiatric Institute and GGZ Delfland. We aim to include a broad range of patients with PD, because this represents the population that is treated within outpatient, specialized mental health care centers for PD the best.

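### Section 11.4 describes EMDR as given on top of usual PD care, which contradicts the EMDR-versus-waiting-list design, and no sentence states the rule on PD treatment for both arms

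*Protocol*

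**What the plan says.** **Design sections.** The Summary describes "two arms: EMDR and no treatment (waiting list"), and section 3 says that "a single-blind RCT with two groups (EMDR versus waiting list) will be performed". Section 5.1 describes the experimental condition as EMDR sessions and mentions no PD care alongside them. Section 5.2, on co-interventions, says only NA.

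**Section 11.4.** After a sentence on the safety of EMDR comes a fragment without a subject: it "is applied in addition to treatment as usual for PD with regular meetings". The next sentence concerns the days after a session in which emotions or intrusions may rise, and says that "patients have the opportunity to discuss their symptoms with the EMDR- and PD-therapists".

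**The waiting rule.** Section 11.4 also says: "The study requires participants in the control group to not receive treatment for three months". The Summary repeats this, again for the control group. For controls, section 5.1 adds: "After three months patients will be offered the opportunity of following a standard treatment for their PD". Section 8.3 item 7 describes the experimental group, then the waiting-list comparison, and then says that patients may choose standard PD treatment after three months. It does not say which patients.

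**The concern.** The protocol gives two accounts of what the EMDR arm receives. In the design sections it is EMDR alone. In 11.4 it is EMDR added to usual PD care. Only the control arm is told in so many words to go without treatment for three months.

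Suppose a patient already in PD care enters and a site follows 11.4. In the EMDR arm that care continues. In the control arm it has to stop. The comparison up to three months is then EMDR plus usual care against nothing, and neither the difference in PD symptoms nor the difference in costs can be assigned to EMDR. Both matter, because section 2 lists effectiveness on PD symptoms and cost-effectiveness as the two primary objectives.

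If usual care is not meant to run alongside EMDR, the fault lies elsewhere. Section 11.4 then describes a safeguard, regular meetings and a PD-therapist, that the trial does not provide.

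**Working it through.** The plan states no figure on this point, so the check is a comparison of texts followed by a count of what is exposed.

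**1. Subject of the fragment.** The sentence before it is about EMDR, and the sentence after it is about the days following an EMDR session. No other subject fits, so I read it as EMDR. This is an inference from context.

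**2. The statements by arm, up to three months.**

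| Source | EMDR arm | Control arm |
|---|---|---|
| Summary, section 3 | EMDR | waiting list; the Summary adds no treatment |
| 5.1 | EMDR sessions; PD care not mentioned | standard PD treatment offered after three months |
| 5.2 | NA | NA |
| 8.3 item 7 | choice of standard treatment after three months, arm not named | same sentence |
| 11.4, fragment and next sentence | EMDR plus usual PD care; PD-therapist available | – |
| Summary and 11.4, no-treatment rule | not named | no treatment for three months |

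The fragment in 11.4 cannot stand beside the Summary, section 3 and 5.1. Section 5.2 can be read as no co-intervention, but it sets no rule. Section 8.3 item 7 would settle the matter if it named both arms.

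**3. Is the fragment isolated?** Not quite. The sentence after it assumes a PD-therapist. The interview guide for EMDR patients (Appendix A) asks how EMDR affected their other treatments, and whether they discussed it in their main treatment. This fits concurrent PD care. But section 8.3 item 6 gives no date for the interview, so it fits PD treatment begun after three months equally well.

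**4. Which patients could be affected.** Section 5.1 says of the three months: "This period is shorter than the regular waiting time for treatment of PD, which ranges 6 to 12 months". New PD care within three months is therefore unlikely in either arm. What remains is care already running at entry. The eligibility criteria (4.2, 4.3) do not mention current PD treatment.

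**5. What is exposed.**
- Post-baseline visits: 5 weeks, 3 months, 6 months and 12 months, so 4.
- Visits up to the end of the no-treatment period: 5 weeks and 3 months, so 2 of 4. All post-baseline visits enter the primary mixed model (10.1).
- Follow-up months in that period: 3 / 12 = 25%.

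**6. Form of the bias.** Let p be the share of EMDR-arm patients who continue PD care, and d the effect of that care by a given visit, in standard deviations, compared with going without it. If the effects add, the bias at that visit is p × d. The protocol gives neither p nor d, so there is no value to compute. The bias is zero if p = 0.

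**The case against.** The strongest reply is that the damaged sentence stands in an ethics narrative, may be leftover text, and is outweighed by the sections that define treatment, which agree with one another. A rule about receiving no treatment can in any case name only controls, since the other arm is being treated. The most natural reading of 8.3 item 7 covers both arms. Section 5.1 compares the three months with the regular waiting time, which suggests patients who have not yet started PD treatment.

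Most of this stands, and it limits the point. Naming controls in a statement of participant burden does not by itself permit usual care in the EMDR arm. But it does not remove the contradiction: the fragment is current text, the sentence after it depends on the same arrangement, and 8.3 item 7 leaves its scope to be inferred.

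A reader might go further and infer that the trial enrols patients already in PD therapy, so that the early results are confounded. The protocol does not support that:

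- Section 4.1 says of its broad range of PD patients that "this represents the population that is treated within outpatient, specialized mental health care centers for PD the best". This justifies diagnostic breadth and says nothing about treatment status at entry.
- Recruitment through a treating therapist or physician (8.3, 11.2) does not establish that PD-specific therapy is under way.
- The Appendix A questions are undated, as noted above.

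A reader might also infer that an asymmetric comparison was chosen. The text shows a conflict of wording, not such a choice.

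**Conclusion.** Wrong as written: the protocol contradicts itself on what the EMDR arm receives. Section 11.4 adds usual PD care with PD-therapists at hand, while the Summary, section 3 and section 5.1 set EMDR against a waiting list. The explicit no-treatment rule names controls only, and 8.3 item 7 probably extends the wait to both arms without saying so.

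The consequence is conditional. It arises only if patients already in PD care are enrolled and 11.4 is followed for them. In that case the 5-week and 3-month contrasts, 2 of the 4 post-baseline visits, and the first 3 of 12 months of costs would compare EMDR plus usual care with nothing. If that care helps, the bias in symptoms would favour EMDR, while the cost of the care would fall on the EMDR arm. The counts describe exposure, not bias, and the bias itself cannot be sized from the protocol.

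This rests on EMDR being the missing subject of the fragment, which the context supports but the text does not state. The correction is worth making because it is cheap and the visits concerned are the only post-baseline ones before controls may start standard treatment.

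**What to change.** - In 5.1 or 5.2, and in 8.3 item 7, state that the same rule applies to both arms: no PD-specific treatment until the 3-month assessment.
- In 11.4, correct or delete the fragment, and name who supports patients if symptoms rise after an EMDR session.

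The cost is an amendment to protocol wording. It needs no new data and no change to the sample size.

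Two additions are optional and not part of this point. A sentence on current PD treatment in the eligibility criteria would make the rule easier to apply, but could narrow the broad population that 4.1 seeks. Tabulating service use from the TiC-P by arm up to three months would make departures visible. That instrument is already planned (8.1.2, 10.2), and the table can be left to the statistical analysis plan.

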**Nature and extent of the burden and risks associated with participation, benefit and group relatedness:** It is expected that patients who receive EMDR, will experience a reduction in PD- and PTSD-symptoms and an improvement in quality of life and interpersonal functioning. In addition, EMDR is safe and not associated with adverse events. The study requires participants in the control group to not receive treatment for three months. In the two or three days after an EMDR-session symptoms of emotion dysregulation or psychotrauma may increase. This effect is temporarily and not associated with any increase in selfinjurious – or suicidal behavior.

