### **5.2 Use of co-intervention**

NA

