## 8.3 Study procedures

1. Patients will be recruited in two ways; 1. by means of posters hanging in the waiting room; patients can announce themselves to their treating therapist/physician or contact the researchers directly 2. Patients with a PD will be informed by the therapist/physician about the study. The therapist/physician informs the researchers, who will send information to the patient by mail and call the patients to invite them for an appointment. Interested patients will receive further information about the study during an appointment with one of the researchers. Furthermore, the researcher will check eligibility for inclusion. At the end of the appointment patients will be given informed consent forms. The patients are allowed to take the time they need to make a decision about participation. Patients who decide to participate will be asked to sign informed consent.
2. Diagnostic instruments before inclusion: a. Any PD diagnosis will be confirmed using the SCID-5-PD
3. Informed consent: During an intake interview with the researchers, patients are informed about the study verbally and formally. If the patient had enough time to consider whether he/she wants to participate into this study, the patient is asked to give written, informed consent.
4. Randomization: After patients are included and have given informed consent, patients are randomized into one of the two conditions.
5. Questionnaires will be administered at baseline (before randomization), after weeks (post EMDR) and three, six and twelve months after onset of the study.
6. Interview: all participants in the EMDR group will be requested to participate in a qualitative interview about their experiences with EMDR therapy.
7. Patients in the experimental group are treated with ten biweekly, ninety minute, EMDR sessions. These patients are compared with a waiting list condition. After three months of follow-up patients can decide whether they want to have standard treatment for PD.

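### Section 11.4 places EMDR on top of usual personality disorder (PD) care, the rest of the protocol describes EMDR sessions only, and no rule on PD care before month 3 covers both arms

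*Protocol*

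**What the plan says.** Section 11.4, in a run of sentences about EMDR, contains one that begins without a subject and says that it "is applied in addition to treatment as usual for PD with regular meetings". The next sentence adds that, if emotions or intrusions rise in the days after a session, "patients have the opportunity to discuss their symptoms with the EMDR- and PD-therapists". The control arm is described differently. Both the Summary and section 11.4 state: "The study requires participants in the control group to not receive treatment for three months". No matching sentence is written for the EMDR arm.

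The sections that define the design do not mention PD care alongside EMDR. The Summary gives "two arms: EMDR and no treatment (waiting list"). Section 3 sets the aim as "To assess the surplus value of EMDR compared to waiting list" and lists ten EMDR sessions over five weeks. The experimental paragraph of section 5.1 lists the same sessions. Section 5.2, headed "5.2 Use of co-intervention", has the single entry NA.

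Standard PD treatment appears in two places. Section 5.1 says, under the control condition: "After three months patients will be offered the opportunity of following a standard treatment for their PD". Section 8.3 item 7, after describing the EMDR sessions and the comparison with the waiting list, says: "After three months of follow-up patients can decide whether they want to have standard treatment for PD".

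**The concern.** What each arm may receive between randomisation and month 3 defines the treatment contrast. It belongs in the protocol and cannot be settled at the analysis stage. The two accounts correspond to two different trials. In one, EMDR is compared with a waiting list. In the other, EMDR plus ongoing PD care is compared with nothing.

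The main outcome in section 10.1 is the number of PD symptoms, which is what PD care is meant to reduce. If such care ran in one arm only, it would be tied to allocation, and the mixed model could not separate its effect from that of EMDR. The economic evaluation has the same problem, because PD care in one arm enters both the incremental costs and the incremental effects.

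**Working it through.** No figure in the protocol is in dispute, so the check is a comparison of the passages.

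**1. PD care in the EMDR arm before month 3**
- Section 11.4: present, as treatment as usual with regular meetings. The subject of the sentence is missing, but the sentences on either side concern EMDR.
- Section 11.4, next sentence: a PD therapist can be reached after a session. This is conditional on symptoms rising, so taken alone it is a safety contact.
- Appendix A, question 7: patients who had EMDR are asked whether it affected their other treatments, and whether they discussed it in their *hoofdbehandeling* (main treatment). This fits the add-on account. Section 8.3 item 6 gives no date for the interview, so the question does not prove that the care ran before month 3.
- Summary, section 3, section 5.1 (experimental condition), section 8.3 item 7: EMDR sessions, with no other care mentioned.
- Section 5.2: NA, which most simply means that no co-intervention is foreseen.

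**2. PD care in the control arm before month 3**
- Summary and section 11.4: none for three months. This is an explicit rule.

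**3. When standard PD treatment is offered**
- Section 5.1: after three months, stated for controls only.
- Section 8.3 item 7: after three months, for patients without naming an arm. It can be read as covering both arms. It can also be read as repeating the offer to controls, since it follows directly on the mention of the waiting list.
- Summary and section 3: silent.

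For the EMDR arm, then, only section 8.3 item 7 could place standard PD treatment after month 3, and only on one of its two readings.

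**4. Which visits are exposed**
There are five assessments: baseline, week 5, and months 3, 6 and 12. Controls are offered treatment after three months. Of the four post-baseline visits, two (week 5 and month 3) precede that offer. These are the visits that can contrast EMDR with an untreated group, and they are the ones affected if section 11.4 is followed.

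**5. Could patients already be in care at entry?**
Section 8.3 item 1 recruits partly through a treating therapist or physician, so some patients in either arm may have a clinician when they enter. The protocol states no common rule for that contact.

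**6. Size**
A bias estimate would need the share of the EMDR arm in PD care before month 3 and the effect of that care over those weeks. The protocol gives neither, so no figure is offered.

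**The case against.** The strongest reply is that the conflict rests on a broken sentence. It has no subject, stands in an ethics section that does not instruct sites, and may be leftover text. Four other places describe EMDR sessions alone, and NA in section 5.2 agrees with them. Section 5.1 gives the regular wait for PD treatment as 6 to 12 months, which makes it less likely that new PD treatment starts before month 3 in either arm. A treating therapist who refers a patient is not necessarily giving PD psychotherapy.

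Much of this stands. A reader might infer that EMDR patients will in fact receive PD care before month 3. The documents do not support that; they show only that two accounts are open. A reader might also infer that the Summary, section 3 and section 5.1 all place standard PD treatment after month 3 for the EMDR arm. They do not, as the comparison shows. Nor does settling the point remove every other explanation for a difference: patients know their allocation, and section 5.1 has controls seen once by a study therapist.

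The reply does not remove the contradiction. The sentence is in the current text, in the benefit and risk assessment, where it describes regular meetings that no other section provides. Appendix A makes it more than a stray slip. The long regular wait does not exclude care already under way at entry. Above all, the no-treatment rule binds one arm only, so nothing in the text prevents the asymmetry.

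**Conclusion.** The point holds as an internal contradiction with a possible consequence for the treatment contrast. If section 11.4 is followed as written, the comparison at week 5 and month 3 is EMDR plus PD care against no treatment, and differences in PD symptoms or costs at those visits cannot be attributed to EMDR alone. If EMDR is given without PD care, this particular confounding does not arise.

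This rests on two assumptions: that EMDR is the missing subject in section 11.4, and that PD care given in one arm would affect PD symptoms or costs. How many patients would be affected is not stated, and the size of any bias is unknown. It should be corrected because the correction is cheap and analysis cannot repair the asymmetry afterwards. No bias has been demonstrated.

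**What to change.** 1. **Section 5.2.** Replace NA with one rule for PD care from randomisation to the month-3 visit that is the same in both arms. The default would be no PD treatment in either arm, with contact with a clinician for safety or in a crisis open to both.
2. **Section 11.4.** Align the add-on sentence and the reference to PD therapists with that rule. Keep the post-session contact as a safety measure.
3. **Section 5.1 and section 8.3 item 7.** Say whether the month-3 offer of standard PD treatment covers both arms or controls only.
4. **Reporting.** Tabulate PD care received, by arm and period, from the TiC-P.

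If PD care alongside EMDR is what the sponsor intends, there are two consistent options. One is to allow it equally in both arms and change the no-treatment rule for controls accordingly. The other is to keep the asymmetry and restate objective 1 and the conclusions as EMDR plus usual PD care versus no treatment.

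The cost is wording in four sections and one table from an instrument already collected. No visits or patients are added and no safety contact is lost. If some EMDR patients are meant to have PD care before month 3, withholding it would be a substantive change for the ethics committee, and one of the two alternatives is then the better route.
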